**10) Ayurvedic Measures: (Appendix I)**

BASELINE:

a) Prakriti

b) Clinical Features

c) Ayurvedic Disease Subsets / Stages

FOLLOW UP / MONITORING:

a) Clinical Features

b) Ayurveda examination

c) Ayurvedic Disease Subsets / Stages

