**n. Statistical statement:**

The design of the drug trial is exploratory in nature. Though a randomized selection of patients will be done to either of the two arms, the sample size is that of convenience (expert opinion) and the same is not statistically powered however, sample size (70 patients in each arm) sufficient to draw meaningful conclusions. The statistical significance p<0.05(two sided) is predefined for analysis. Statistical analysis will be performed using standard tests to compare the two interventional arms for primary and secondary efficacy measures. Safety events will be also analyzed. Both intent-to-treat and per protocol completer analysis will be performed. Regression analysis will be done to identify predictors of response.

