**11.2 Secondary Efficacy:**

1) Rate of patients with negative SARS-CoV-2 on nasal or throat swab in a 2-day continuous real time RT-PCR test beginning from ‘first day of clinical recovery’ (see above) or ‘Day 10 after onset of symptoms depending on whichever of the two time points is first achieved

2) Timelines (days counted from onset of illness) - normal body temperature <37◦C, absence or minimal cough (see ‘clinical recovery’ for the definition), absence of dyspnoea (respiration rate 24/minute or less on room air), onset of clinical pneumonia, pneumonia diagnosed on chest X-Ray or CT scan, time to supplemental oxygen, admit in intensive care unit, mechanical ventilation (non-invasive), mechanical ventilation (invasive), steroid use, respiratory failure, adult respiratory distress syndrome, cytokine storm syndrome, secondary infection, shock, septicaemia shock, hospital discharge, death, negative nose or throat swab confirmatory test, all-cause mortality (Time Frame: up to 28 days).

Note: In case of symptoms, the absence on improvement should be sustained for at least 72 hours or live hospital discharge, whichever comes first.

3) Proportion OF patients developing an event that reflects clinical or otherwise improvement of worsening (the events are similar to those listed under Timelines, see above)

4) Improvement on pulmonary function tests using simple ‘home expiratory spirometer’ device and peripheral pulse oximetry

5) Improvement in selected laboratory parameters: blood haemoglobin, differential and total leukocyte counts, liver enzymes, renal functions, acute phase reactants, serum IL-6 and other selected cytokines, serum muscle enzymes (CK, CPK), serum ferritin, serum d-Dimer, anti-oxidant markers, serum BNP (cardiac function)

6) Serological Protective Antibody Assay (IgM and IgG)

7) Radiological Improvement on digital chest Xray and HRCT chest

8) Drug related: side effects and toxicity, and tolerability

9) Health status: WHO QOL (Appendix M) brief, health related behaviour habit and fitness questionnaire based on visual analogue scale (See Appendix N)

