**17.2 Statistical Analysis:**

Whenever suitable, both completer and an intent-to-treat analysis with ‘last observation carried forward’ will be performed; for intent-to-treat analysis the patient should have completed at least 4 weeks of intervention and completed the follow up visit at 4 weeks post enrollment.

All statistical processing will be performed using SPSS & BMDP software unless otherwise stated.

The data will be individually analyzed for central tendencies (mean, median), range, standard error, standard deviation and 95% confidence intervals for each intervention arm in each of the groups in the study. Data will be tabulated and graphically shown using standard format and MS Excel and other software programs. Though ANOVA will be used for most of the measures, standard parametric (Student t-test) and non-parametric statistical tests (Mann Whitney statistic, Kruskal Wallis test) will be used depending upon the normality of the data. Fisher’s exact test or Chi Square will be used to test the proportion of patients classified as efficacy failures and those with AE (calculate exact binomial 95% Confidence Interval).

The primary efficacy measures of ‘mean time to clinical recovery’ and ‘proportion of patients with clinical recovery’ in the two arms will be compared using appropriate statistical tests; ANOVA for ‘mean time’ and two proportion z-test for proportion of patients.

Secondary efficacy measures in the two arms will also be compared and Bonferroni correction will be applied for multiple comparisons.

Risk ascertainment will be done for selected variables. Regression analysis (multivariate and step down) will be used to identify predictors for important outcomes. Survival analysis will be carried out to compare the two interventions (HCQ and Ashwagandha) for primary efficacy at different study time points.

Within arm efficacy will be evaluated by a one sample Student t-test.

Significance for each statistical test result will be considered at two-sided p< 0.05.

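### Bonferroni is promised for the secondary comparisons, but the family is not fixed and the plan does not say that p<0.05 applies to adjusted p-values, so the per-test threshold could be 0.05, 0.0056 or about 0.0007

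*Combined protocol and SAP*

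**What the plan says.** Section 17.2 (Statistical Analysis) commits to a correction: "Secondary efficacy measures in the two arms will also be compared and Bonferroni correction will be applied for multiple comparisons". It names neither the measures in the family, nor their number, nor an adjusted threshold. Its last sentence is general: "Significance for each statistical test result will be considered at two-sided p< 0.05".

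Item n of the Study Synopsis says "The statistical significance p<0.05(two sided) is predefined for analysis" and then, as a separate sentence, "Statistical analysis will be performed using standard tests to compare the two interventional arms for primary and secondary efficacy measures". It does not mention Bonferroni.

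The list to be corrected is in Section 11.2. It has nine numbered items, the last being "9) Health status: WHO QOL (Appendix M) brief, health related behaviour habit and fitness questionnaire based on visual analogue scale". Item 8 is side effects and tolerability, so there are eight efficacy items. The synopsis adds a tenth: "10) Ayurvedic Measures: (Appendix I)". Several items are bundles. Item 2 lists 20 event times, and item 3 compares the arms on proportions with such events ("the events are similar to those listed under Timelines, see above"). Item 5 is open-ended, because it includes other selected cytokines and anti-oxidant markers without naming them.

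**The concern.** Bonferroni is defined only once the number of comparisons is fixed. Here that number can be read in several ways, and the closing sentence of 17.2 can be taken to mean an unadjusted 0.05 for every test. A secondary p-value of 0.02 is significant only if 0.05 applies to the raw value. A p-value of 0.003 is also significant under a nine-item family, but not under one of 75. Nothing in the plan settles which applies, so the choice could be made after the data are seen. The same text governs three separate drug trials, so the question arises three times.

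**Working it through.** The plan states no family size and no adjusted threshold, so there is no figure to reproduce. The check is a count, a division and a power calculation.

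**1. Counting the family at one time point.**

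| Section 11.2 item | Low count | High count |
|---|---|---|
| 1. RT-PCR negativity | 1 | 1 |
| 2. Event times (19 in the synopsis, 20 in 11.2, where death and all-cause mortality are listed separately) | 19 | 20 |
| 3. Event proportions, if the same events | 19 | 20 |
| 4. Spirometry, oximetry | 2 | 2 |
| 5. Laboratory: 13 named groups, or single analytes | 13 | 27 |
| 6. IgM, IgG | 2 | 2 |
| 7. X-ray, HRCT | 2 | 2 |
| 8. Safety | 0 | 1 |
| 9. Two questionnaire totals, or WHOQOL-BREF plus nine visual analogue scales | 2 | 10 |
| **Total** | **60** | **85** |

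The 27 analytes are haemoglobin 1, total and differential leukocytes 2, liver enzymes 3, renal 2, acute phase reactants (ESR, CRP) 2, cytokines 11 (the Section 13 panel), CK 1, ferritin 1, D-dimer 1, SOD and GSH 2, BNP 1. With the nine cytokines in the Appendix A footnote the total is 25 analytes. Using 20 events, 25 analytes, two questionnaire totals and the safety item gives 1 + 20 + 20 + 2 + 25 + 2 + 2 + 1 + 2 = 75, which serves below as a middle value.

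**2. Per-test threshold, 0.05/k.** k = 8: 0.00625. k = 9: 0.0056. k = 60: 0.00083. k = 75: 0.00067. k = 85: 0.00059. From nine items to 75 comparisons the threshold falls by a factor of 75/9 = 8.3. These values need no assumption beyond the count.

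**3. What the threshold costs in power.** Section 17.1 gives 70 per arm, says no power calculation was done, and expects 15–20% withdrawal; 70 × 0.80 = 56. The effect size is my assumption. The calculation is a two-sided two-sample t-test with noncentrality d√(n/2) and 2n − 2 degrees of freedom. For d = 0.5 and n = 70 the noncentrality is 0.5 × √35 = 2.96, against critical values of 1.98 (k = 1), 2.82 (k = 9) and 3.48 (k = 75).

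| Assumed effect (SD) | n per arm | 0.05 unadjusted | k = 9 | k = 75 |
|---|---|---|---|---|
| 0.4 | 70 | 65% | 33% | 14% |
| 0.5 | 70 | 84% | 56% | 31% |
| 0.6 | 70 | 94% | 77% | 53% |
| 0.4 | 56 | 56% | 24% | 9% |
| 0.5 | 56 | 75% | 43% | 20% |
| 0.6 | 56 | 88% | 64% | 38% |

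**4. False positives if 0.05 were applied to raw p-values.** For independent tests the chance of at least one is 1 − 0.95^k: 37% for k = 9 and 98% for k = 75. With an assumed common correlation of 0.5 (simulation) it is about 27% and 71%; at 0.8 it is about 16% and 33%.

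**The case against.** The strongest reply is that there is no conflict. Section 17.2 makes a specific provision for the secondary measures and then a general statement of level, and 0.05 is simply what Bonferroni divides, or what adjusted p-values are compared with. That reading is reasonable. A reader might infer that the plan contradicts itself, or that it intends to test the secondaries uncorrected. The documents do not support either inference: the synopsis is silent on the correction and does not exclude it, and its 0.05 sentence is separate from the one about comparing the arms. The false-positive rates in step 4 therefore describe only the unadjusted reading and are not a property of the plan. The reply does not supply the family, however; with 0.05 granted as the family-wise level, the threshold still varies about eightfold.

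A reader might also infer that correcting over the whole list leaves almost no power. At 0.5 SD the figure is 31% with 70 per arm and 20% with 56: a large loss, but not that.

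Three further points stand. The count is a reading of the list: item 3 says only that its events are similar to the timelines, and the family would be three if only weeks 4, 8 and 12 within a measure were corrected. Repeat visits do not multiply the whole list, because the timelines have a 28-day frame and Appendix A schedules no imaging at weeks 4, 8 or 12. And a comparison of two means does not represent the event times and proportions, which are at least half of the count.

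The exploratory label lowers the stakes. It does not settle the rule, since the plan itself chose to correct and to set a significance level.

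**Conclusion.** The concern holds as an incomplete specification. The plan commits to Bonferroni for the secondary comparisons but does not define the family or say that 0.05 applies to adjusted p-values. On the text as it stands the per-test threshold could be 0.05, 0.0056 or about 0.0007. That span depends only on how the list is counted; the power figures also rest on an assumed effect and a comparison of means. The primary analysis is not affected, but any secondary claim of significance is. This should be corrected, and it is also an opportunity: Holm gives the same 5% family-wise error as Bonferroni and is never less powerful.

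**What to change.** In Section 17.2:

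- Replace Bonferroni with Holm. With m measures, compare the smallest p-value with 0.05/m, the next with 0.05/(m − 1), and so on, stopping at the first failure.
- List the secondary measures in the family, each as one variable at one time point. The sponsor should choose them from endpoints and time points already in the schedule, so that no new composite or visit is needed.
- Count each event once, either as a time or as a proportion, and treat death and all-cause mortality as one.
- Report all other secondary measures as estimates with 95% confidence intervals, labelled exploratory, with no significance claims.
- State, here and in item n of the synopsis, that for secondary measures 0.05 applies to the adjusted p-values.

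Holm's first step is the same as Bonferroni's, so most of the gain comes from a short list. As an illustration only, four measures would give a strictest step of 0.05/4 = 0.0125, where power for 0.5 SD is 67% with 70 per arm and 54% with 56.

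The cost is wording only, with no new data. There are two downsides: measures outside the list can no longer be called statistically significant, and simultaneous confidence intervals are less simple under Holm than under Bonferroni.

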**l. Laboratory investigations:**

These are common to the each of the three Ayurveda formulation drug trials:

1. Haemogram, Platelet count, Total leukocyte differential count, Hemoglobin and ESR,
2. Liver function test - Serum Bilirubin, ALT, AST, Alkaline phosphatase,
3. Kidney Function Test ( Serum creatinine, Blood Urea Nitrogen)
4. Lipid profile (Total cholesterol, HDL cholesterol, LDL cholesterol, Triglycerides, VLDL)
5. Blood Sugar Level
6. Urine Routine
7. C-Reactive protein titer
8. LDH, Ferritin
9. Pro-Cal
10. CK, B-type natriuretic peptide (BNP), Troponin, D-Dimer
11. Serum Electrolytes (Sodium, Potassium, Chloride, Iron, Zinc, Manganese) Vitamin D, B12
12. Oxidation Biomarkers-Superoxide Dismutase (SOD), Glutathoine (GSH)
13. Cytokine Panel (Interleukin-2, Interleukin l - 4, Interleukin-6, Interleukin-10, TNF-α, Interleukin-1β, Interleukin-13), Monocyte Chemotactic Protein (MCP), Gamma Interferon. RATIONALE FOR CYTOKINE ASSAY: Cytokine assay can be used to study important anti-viral effects (gamma interferon), immune mediated inflammation (IL-6, anti-TNF, IL-17), TH 1 and TH 2 immune response and antibody producing B cell activity (IL4, IL13), activation of immune cells such as macrophage activation (MCP). Intense up regulation and elevation of IL 6 and several other cytokines has been reported by several clinical case series and research in COVID-19 and can guide specific therapy (as in case of use of monoclonal antibody to IL-6 receptor being used to treat Cytokine storm in COVID 19)
14. Serum Immune Response tests (IgG and IgM) for COVID-19
15. Urine Pregnancy Test for women of child bearing potential

Other Investigations:

1. USG Abdomen and Pelvis
2. Color Doppler and 12 Lead ECG
3. Chest X-ray
4. HRCT Chest

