**SECONDARY**

1. To determine the therapeutic effect of a combination of SOC plus a selected standardized Ayurvedic drug on surrogate markers of COVID-19 disease severity and complications, and recovery pertaining to broad based domain of acute phase reactants, pro-inflammatory cytokines, imaging assessment, anti-oxidant activity, organ dysfunction and damage
2. To determine the early and late post-recovery health benefits of a combination of selected standardized Ayurvedic drug plus SOC using qualitative measure of health status (WHO Quality of life assessment questionnaire) and health related behaviour, habits and fitness questionnaire
3. To describe the clinical profile of COVID-19 with special reference to early symptoms, severity of disease, complications, course of disease, diagnostic investigations, biochemical and imaging abnormalities, patterns of recovery
4. To determine the predictors of early and late recovery from COVID-19 using a therapeutic combination of SOC plus a selected standardized Ayurvedic drug

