**17.1 Sample Size:**

A convenience sample size of 70 patients in each of the arm is selected. The total sample size will be 140 patients in each of the 3 studies. The sample size is not based on any power calculations but by consensus within the experts of the Working Group constituted for the purpose of this protocol. It is assumed that the withdrawal rate may be in the range of 15-20%.

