**BASELINE SYMPTOMS: (OF ANY ETIOLOGY)**

|  | NO | YES | IF YES, DESCRIBE |
| --- | --- | --- | --- |
| Headache |  |  |  |
| Disturbed sleep |  |  |  |
| Anorexia |  |  |  |
| Oral Ulcers |  |  |  |
| Retrosternal Burning or Discomfort |  |  |  |
| Poor Digestion |  |  |  |
| Eructation |  |  |  |
| Constipation |  |  |  |
| Altered Bowel Habits |  |  |  |
| Body ache |  |  |  |
| Tingling numbness |  |  |  |
| Itching |  |  |  |
| Skin rash |  |  |  |
| Irregular menses |  |  |  |

Physical Examination (Please tick)

|  | Normal | Abnormal | If Abnormal, please comment |
| --- | --- | --- | --- |
| General Appearance | **□** | **□** |  |
| Skin | **□** | **□** |  |
| Head, Neck & Thyroid | **□** | **□** |  |
| Eyes | **□** | **□** |  |
| Nose and Throat | **□** | **□** |  |
| Lymph Nodes | **□** | **□** |  |
| LUNGS | **□** | **□** |  |
| Cardiovascular | **□** | **□** |  |
| Abdomen | **□** | **□** |  |
| Central Nervous System | **□** | **□** |  |
| Others – Specify | **□** | **□** |  |
|  | **□** | **□** |  |
|  | **□** | **□** |  |

Remarks: ________________________________________________________________________

________________________________________________________________________________

________________________________________________________________________________________________________________________________________________________________________________________________________________________________________________

Completed by: __________________________

Signed _________________________________

Dated : _________________________________

Please see Inclusion Exclusion Criteria on reverse

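### Step-down regression at p<0.05, with no candidate list, correction or validation, is a weak basis for naming predictors of recovery

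*Combined protocol and SAP*

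**What the plan says.** Section 17.2 (Statistical Analysis) plans the search in one sentence: "Regression analysis (multivariate and step down) will be used to identify predictors for important outcomes". The outcomes meant are not listed and no candidate variables are named. The section closes with a general rule: "Significance for each statistical test result will be considered at two-sided p< 0.05". Its only multiplicity statement is "Secondary efficacy measures in the two arms will also be compared and Bonferroni correction will be applied for multiple comparisons", which concerns comparisons between arms.

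The search serves a stated objective. Secondary objective 4 in section 4 is "To determine the predictors of early and late recovery from COVID-19 using a therapeutic combination of SOC plus a selected standardized Ayurvedic drug". Synopsis item c words it differently, as predictors of drug response, and synopsis item n again refers to regression for predictors of response.

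On size, section 17.1 says "The total sample size will be 140 patients in each of the 3 studies", that is 70 per arm, and adds "It is assumed that the withdrawal rate may be in the range of 15-20" per cent.

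**The concern.** Step-down selection starts from a set of candidates, removes the least significant term, refits, and stops when everything left passes the threshold. The surviving p-values are then read as if those terms had been chosen in advance. They were not, so the p-values are too small and the coefficients tend to be too large. The more candidates that enter, the more likely it is that something survives by chance.

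The plan does not limit how many enter, and the forms offer many. If the list is long, secondary objective 4 and synopsis objective (ii) could be answered with chance findings presented as predictors. Nothing in the plan, such as a correction, shrinkage or internal validation, would let a reader tell the difference.

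**Working it through.** The plan states no error rate, candidate count or power for this search, so there is no figure of its own to reproduce.

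**Inputs from the documents**

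- Patients: 140 with both arms. Objective 4 is worded for the combination arm, so n may be 70.
- Withdrawal of 15–20% leaves 140 × 0.85 = 119 to 140 × 0.80 = 112 patients.
- Threshold: 0.05, two-sided.
- Variables collected at baseline: synopsis item l lists about 46 blood analytes, leaving out urine tests and counting the differential count as one. Nine come from "Cytokine Panel (Interleukin-2, Interleukin l - 4, Interleukin-6, Interleukin-10, TNF-α, Interleukin-1β, Interleukin-13), Monocyte Chemotactic Protein (MCP), Gamma Interferon". The case record form in Appendix H has 14 items under "BASELINE SYMPTOMS: (OF ANY ETIOLOGY" and 11 named concomitant illnesses. That is 46 + 14 + 11 = 71 before vital signs, demographics, Prakriti, the Ayurvedic features, the 26 WHOQOL-BREF items and the 9 HR-BHF items.

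**Assumption.** The number k of candidates entering the model is not in the documents, so results are shown over a range.

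**Step 1, simple formula.** For k independent null candidates each tested at 0.05, P(at least one false positive) = 1 − 0.95^k. This passes one half at k = ln 0.5 / ln 0.95 = 13.5, so at 14 candidates.

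**Step 2, simulation.** Backward elimination in linear regression, with independent standard normal candidates and an outcome unrelated to all of them. The least significant term is removed until all remaining have p<0.05.

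| k | 1 − 0.95^k | At least one kept, n = 70 to 140 | Mean number kept |
|---|---|---|---|
| 10 | 40.1% | 41–45% | about 0.55 |
| 14 | 51.2% | 52–54% | 0.7–0.8 |
| 20 | 64.2% | 64–68% | 1.1–1.3 |
| 40 | 87.1% | about 90% | 2.6 (n = 140), 3.7–3.8 (n = 70) |

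Simulation error is about √(0.4 × 0.6 / 1500) = 1.3 percentage points at 1,500 runs. Single runs therefore stray a little: one at n = 112, k = 10 gave 39%, and one at n = 140, k = 14 gave 50.5%. At k = 12 the rate was 47% at both n = 70 and n = 140. At k = 46, the laboratory list alone, it was 92.5% at n = 140 and 90% at n = 70.

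**Step 3, sensitivity.**

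- Correlated candidates: at n = 140, k = 20, the rate was 65% with pairwise correlation 0.3 and 75% with 0.6.
- Cox models (500 runs per setting): at n = 70, 57% with 14 candidates and 72% with 20; at n = 140, 53% and 70%.
- Logistic models at n = 140 (500 runs per setting): 47% with 14 and 64% with 20 when half the patients have the event; 46% and 62% when 80% do. Here one half is passed between 14 and 20 candidates.

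**Step 4, apparent fit under the null.** The mean R-squared of the selected model was 0.22 at n = 70 with k = 40, but 0.09 at n = 140 with k = 40, and 0.03–0.06 at k = 14.

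**The case against.** The strongest reply is that k is unknown. The plan never says that everything collected goes into the model, and it cannot: the full tally exceeds 140 variables once the Ayurvedic features are counted, and ordinary backward elimination cannot start with more terms than patients. Some prior selection is unavoidable. With about 12 or fewer candidates the false-predictor rate is below one half. This stands, and it limits the conclusion to a conditional one. It does not remove the gap, because prior selection made after seeing the data and left unrecorded is a further source of bias.

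Second, the 0.05 stay rule is inferred. Section 17.2 gives no retention threshold for step-down, and its wording could also cover a full multivariable model reported alongside. This stands in part: 0.05 is the only threshold in the plan and is said to apply to each test. A looser stay rule would keep more noise terms.

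Third, the trial is called exploratory in its title, synopsis and section 17. That lowers the consequence but not the error rate. Synopsis item n also calls the sample sufficient for meaningful conclusions, and the regression is described as identifying predictors rather than suggesting them.

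Fourth, the simulation assumes that nothing predicts. The protocol's own literature review links older age, comorbidity, D-dimer, ferritin and IL-6 with severe or fatal disease, so a complete null is the worst case. This stands.

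**Conclusion.** The concern holds in conditional form. The plan uses an unrestricted selection method, with p<0.05 as its only threshold, to answer a secondary objective, and gives the reader no means of judging what it returns. If no candidate predicts, the chance of at least one false predictor runs from about 41–45% with 10 candidates to about 90% with 40, for one outcome in one trial. Several outcomes and three trials add further chances. These figures rest on an assumed k, an inferred stay rule, a complete null, and linear models with independent normal candidates; the Cox and logistic checks give broadly similar rates.

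A reader might infer more: that the whole collected set will be searched, that most trials will therefore report a false predictor, or that the rule returns predictors whether or not any exist. The documents do not support this. They do not state what enters the model, and on the figures above an analysis with 10 null candidates returns nothing more often than not. Nor is a convincing apparent R-squared a general feature: 0.22 appears only at n = 70 with 40 candidates. The primary comparison between arms does not depend on this analysis. The point is worth correcting but does not threaten the main result.

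**What to change.** In section 17.2, delete the step-down procedure and name the outcomes to be modelled. Pre-list about 6–8 baseline variables already collected, for example age, sex, days since onset, mild disease versus pneumonia, any comorbidity, baseline SpO2 and CRP. Fit them together in one model without selection, with treatment arm included when both arms are used, and report every coefficient with its 95% confidence interval.

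For predictors of drug response, report treatment-by-covariate interactions for the same list in the two-arm data. A model without them can show only who recovers sooner, not who benefits from the drug.

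A wider search over laboratory, cytokine or Ayurvedic variables can remain if it is labelled hypothesis-generating and uses a penalised model with bootstrap optimism correction.

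A pre-listed model is not free of chance findings: with 6 to 8 null terms, 1 − 0.95^6 = 26.5% to 1 − 0.95^8 = 33.7% of analyses would show at least one nominal p<0.05, by the independence formula. The gain is that the list is fixed, every term is visible and the intervals are not distorted by selection. Bonferroni over the list is optional: with seven terms the bar becomes 0.05 / 7 = 0.007, which costs power, and it is not essential when all coefficients are shown.

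The cost is a change of wording and of software output, with no new data. Fewer variables can be named as predictors, and the interaction estimates will be imprecise with 140 patients or fewer.

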# 8. STUDY DURATION, FOLLOW- UP SCHEDULE AND PROCEDURES

This is summarized in Figure 1 and Table 1. There are several foot notes provided in Table 1 to further clarify a particular event/test procedure and often with particular reference to the role of the study investigator. Several of the clinical events with reference to clinical examination, study record forms and questionnaires, study procedures, laboratory diagnostics and assessments are elaborated in Appendices enclosed with the protocol (Appendix A to S).

It should be noted that this is a study treatment protocol and that the time to outcome in terms of recovery following onset of illness and/or admission to hospital is a varying parameter. The large majority of study patients are expected to recover completely but based on prior knowledge the mortality of COVID-19 in severe case in well documented (see literature review, section above). It is expected that the majority of patients will recover and be discharged to home within 5 days to 15 days of hospitalization.

However, all study patients who recover are required to follow with the study investigators on pre-determined time points as shown in Table 1.

The total duration of the study is 12 weeks and includes the duration of treatment and post clinical recovery or post-hospital discharge period to ensure optimum recovery and regain of health status.

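### Section 17.2 treats a one-sample t-test in each arm as an efficacy test, and names no baseline covariate for the between-arm comparison of continuous secondary measures

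*Combined protocol and SAP*

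**What the plan says.** Section 17.2 sets out four things that matter here.

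- For each arm on its own: "Within arm efficacy will be evaluated by a one sample Student t-test". It names neither the measures nor the null value, and it does not call the result descriptive.
- Between arms, for most measures: "Though ANOVA will be used for most of the measures, standard parametric (Student t-test) and non-parametric statistical tests" are to be used according to normality. For the primary measures it specifies "ANOVA for ‘mean time’ and two proportion z-test for proportion of patients". No baseline covariate is named in any treatment comparison; regression appears only as a search for predictors of outcome.
- For secondary measures: "Secondary efficacy measures in the two arms will also be compared and Bonferroni correction will be applied for multiple comparisons".
- For all tests: "Significance for each statistical test result will be considered at two-sided p< 0.05".

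Section 17.1 gives the size: "A convenience sample size of 70 patients in each of the arm is selected", chosen by consensus and not by a power calculation, with 15-20% withdrawal assumed. Section 8 describes the expected course: "The large majority of study patients are expected to recover completely". Section 2 puts recovery from mild infection at about two weeks. Section 15.1 and Appendix A schedule laboratory tests and the health questionnaires at baseline as well as during follow-up.

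**The concern.** Patients are enrolled while acutely ill and are reassessed at weeks 4, 8 and 12, by which time most should be well. Any change from baseline within an arm combines natural recovery, standard of care and the study drug. A one-sample test of that change asks whether patients got better, not whether the drug helped.

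The wording makes misuse possible. The section labels the test as one of efficacy, and states Bonferroni only in the sentence on between-arm comparison of secondary measures, so no multiplicity control is stated for the within-arm tests. The secondary objectives in Section 4 on surrogate markers and post-recovery health speak of determining the effect of the combination, without naming a comparator. Several measures in Section 11.2 are worded as improvement. A significant within-arm change could be reported as the answer to such an objective.

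The second matter is precision. The sample is unpowered and will lose some patients. If the between-arm analysis of a laboratory value or questionnaire score leaves out its baseline value, or uses it only through a change score, it gives up precision that has already been paid for.

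**Working it through.** **The plan's own figure.** 2 × 70 = 140 per drug trial, as stated. The documents give no effect size, SD or power, so nothing further can be reproduced. Withdrawal of 15-20% leaves 70 × 0.85 = 59.5 to 70 × 0.80 = 56 per arm.

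**Step 1: within-arm test, inactive drug.** Inputs from Section 17: n = 70 (or 56) and two-sided alpha 0.05. Assumptions: the null is zero change from baseline, and natural improvement equals d SDs of change. The test statistic follows a non-central t with n − 1 degrees of freedom and non-centrality d√n. At n = 70, √70 = 8.367, so d = 0.1, 0.3 and 0.5 give non-centralities of 0.84, 2.51 and 4.18.

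| Natural change (SD of change) | Significant, n = 70 | Significant, n = 56 |
|---|---|---|
| 0.1 | 13% | 11% |
| 0.2 | 38% | 31% |
| 0.3 | 70% | 60% |
| 0.4 | 91% | 84% |
| 0.5 | 98.5% | 96% |
| 0.8 | about 100% | about 100% |

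The rate reaches 95% at 0.44 SD (n = 70) or 0.49 SD (n = 56).

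**Step 2: the same data between arms.** Simulation of 10,000 trials with identical arms, 70 per arm, baseline-outcome correlation 0.5:

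| Natural change | Within drug arm | Within SOC arm | Between arms |
|---|---|---|---|
| 0.3 | 69.4% | 69.6% | 4.9% |
| 0.5 | 98.5% | 98.6% | 5.1% |
| 0.8 | 100% | 100% | 5.1% |

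**Step 3: if the two within-arm results were set side by side.** With identical arms and rejection rate p in each, the drug arm alone is significant with probability p(1 − p). At 0.1 SD this is 0.131 × 0.869 = 11%. It peaks near 0.24 SD at 0.508 × 0.492 = 25%. At 0.5 SD it is 0.985 × 0.015 = 1.5%, because both arms then reject.

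**Step 4: baseline adjustment of a continuous secondary measure.** Let ρ be the correlation between baseline and follow-up. It is not in the documents, so 0.3 to 0.7 is assumed, with equal SDs at the two times. Relative variances are 1 for follow-up-only ANOVA, 2(1 − ρ) for change scores and 1 − ρ² for ANCOVA. ANCOVA relative to change scores is therefore (1 − ρ²)/[2(1 − ρ)] = (1 + ρ)/2.

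| ρ | ANCOVA vs follow-up only | 70 per arm acts like | ANCOVA vs change score |
|---|---|---|---|
| 0.3 | 0.91 (9% less) | 70/0.91 = 77 | 0.65 (35% less) |
| 0.5 | 0.75 (25% less) | 70/0.75 = 93 | 0.75 (25% less) |
| 0.7 | 0.51 (51% less) | 70/0.51 = 137 | 0.85 (15% less) |

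The third column is relative to follow-up-only ANOVA. For an assumed true difference of 0.4 SD at 70 per arm, power rises from 66% with follow-up-only ANOVA to 70%, 78% or 91% at ρ = 0.3, 0.5 or 0.7.

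**The case against.** The strongest reply is that the plan does not rest on the within-arm test. The primary objective in Section 4 is comparative, both primary measures are compared between arms, and so are the secondary measures, with Bonferroni. A reader might infer that the plan would declare any inactive drug effective. The documents do not support that: the between-arm tests hold their error rate near 5%, and the control arm passes the within-arm test as often as the drug arm. Nor do they plan to contrast a significant result in one arm with a non-significant one in the other. Step 3 shows only what such a contrast would do if someone made it.

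A near-certain false result across all secondary measures does not follow either. The rate depends on how far each marker moves, and Section 8 speaks of clinical recovery, not of markers. Table 5 suggests that many listed markers are normal in most patients: creatinine was abnormal in 2-10%, and procalcitonin in 5-9% in four of five cohorts. Other secondary measures, such as timelines and event proportions, have no change from baseline to test.

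It is also fair to say that omission of the baseline value is read from silence. Section 17.2 does not say whether "Though ANOVA will be used for most of the measures" means ANOVA on follow-up values, on change, or with a covariate, and the word improvement in Section 11.2 may point to change scores. Unadjusted comparison of randomised arms is valid, and the trial is declared exploratory.

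These points limit the size of the concern but do not remove it. The within-arm test is still labelled as efficacy and held to p<0.05, and ANCOVA is more precise than either reading of ANOVA in Step 4.

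**Conclusion.** The concern holds in two limited parts.

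1. The within-arm test cannot serve as evidence of efficacy in an illness from which most patients recover. Its chance of significance for an inactive drug runs from 13% to 98.5% at n = 70 as natural change goes from 0.1 to 0.5 SD. This rests on an assumed null of zero change and assumed sizes of natural change; the documents give neither.
2. The plan should say how baseline values enter the between-arm analysis of continuous secondary measures: laboratory values, WHOQOL-BREF and the health behaviour questionnaire. The gain from ANCOVA is 9-51% of variance against follow-up-only ANOVA, or 35-15% against change scores, for assumed ρ of 0.3-0.7.

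A reader might extend the second part to the primary analysis. It does not reach that far: time to clinical recovery and proportion recovered have no baseline value of their own. The validity of the primary comparison is not touched by either part. The change should be made, but the defect lies in the specification and interpretation of secondary results.

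**What to change.** In Section 17.2:

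- Remove the within-arm efficacy test, or replace it with within-arm mean changes and 95% CIs, labelled descriptive and without p-values.
- State that every efficacy statement rests on the between-arm difference with its 95% CI.
- Analyse each continuous secondary measure by ANCOVA with terms for arm and the baseline value of that measure. Baseline severity (mild or moderate), recorded in Appendix H, may be added.

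No new data or patients are needed, since the baseline values are already scheduled in Section 15.1 and Appendix A. The cost is a little programming and, because Section 17.2 is protocol text, an amendment agreed by the investigators and ethics committees under Section 19.9.
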